Does learning the Bhagavad Gita reduce psychological distress in people experiencing homelessness	The immediate post-intervention, delayed post-intervention, and long-term follow-up Kessler psychological distress scale scores will be significantly lower than baseline Kessler psychological distress scale scores	54 participants each in the Bhagavad Gita group, Kuchipudi dance group, Both Bhagavad Gita and Kuchipudi dance group, and Control group for 80% power and 5% alpha	The within-group differences will be analysed by repeated measures analysis of covariance, with continued practice and religion as covariates. Subgroup analyses will be conducted by stratifying the participants in each group by age, religion (Hindu, Non-Hindu), educational attainment, and employment. Post-hoc power analyses will be conducted to verify the robustness and reliability of the subgroup analyses	If we find significant within-group differences in the Kessler psychological distress scale scores, it would suggest that learning the Bhagavad Gita has a potential impact on reducing psychological distress in people experiencing homelessness. Additionally, if our subgroup analyses reveal significant differences based on age, religion, educational attainment, and employment, it would imply that the intervention’s effectiveness varies across these subgroups

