Does continued practice influence the effect of the interventions in people experiencing homelessness	The decrease from baselines to delayed post-intervention and long-term follow-up Kessler psychological distress scale scores will be significantly larger in all intervention groups in participants who continue the practices learned during the intervention compared to that in participants who do not continue the practices learned during the intervention	54 participants each in the Bhagavad Gita group, Kuchipudi dance group, Both Bhagavad Gita and Kuchipudi dance group, and Control group for 80% power and 5% alpha	Participants in each group will be subdivided based on whether or not they continued practice during each follow-up. Repeated measures analysis of variance will be conducted on the subgroups	If our hypothesis holds true, it would suggest that sustained practice contributes to greater psychological well-being. Conversely, if there are no significant differences in the decrease of the Kessler psychological distress scale scores between participants who continue and those who do not continue the practices, it would indicate that continued practice does not play a significant role in the effectiveness of the interventions

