### Outcomes and measures

The primary outcome is psychological distress measured by the Kessler scale of psychological distress (K10) in this study. The K10 is a 10-item questionnaire that measures psychological distress based on questions about anxiety and depressive symptoms. It has previously been used in research conducted with PEH [17, 18]. At the immediate post-intervention, delayed post-intervention, and long-term follow-up measurements, apart from the K10, the participants will be asked if they have continued practicing the techniques learned during the intervention (Kuchipudi group: continued practice of the choreography, Gita group: continued self-reflection on the teachings of the Bhagavad Gita, Both group: continued practice of the choreography and continued self-reflection on the teachings of the Bhagavad Gita, and control group: none). The study flowchart is presented in Fig 2.

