### Statistical methods

#### Data analysis

All results will be reported in accordance with the CONSORT guidelines to ensure comprehensive and transparent reporting of the trial’s outcomes. Descriptive summaries of baseline characteristics will be presented to provide an overview of the study population. The comparisons will be between each intervention group and the control group, as well as within each intervention group over time. The repeated measures data will be analysed using the generalised estimating equation (GEE) framework. For the analysis of the primary outcome using the GEE framework, robust standard errors will be used to account for correlated data. Pairwise post-hoc comparisons will be conducted to identify specific group differences. To control for the risk of type I error in these multiple comparisons, the Bonferroni correction will be applied. Subgroup analysis will be conducted using analysis of covariance (ANCOVA) or non-parametric ANCOVA [19] depending on the normality of the data; this may include stratification by age, educational attainment, religion, and employment status. Multiple comparisons will also be addressed using appropriate statistical corrections. These may include the Bonferroni correction, Holm’s adjustment, or the Benjamini-Hochberg procedure, depending on the specific comparisons and the number of tests conducted. The data analysis will be conducted using Python 3.9.13. Statistical significance will be set at a two-tailed p < 0.05.

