#### Sample size calculation

The required sample size for GEE was calculated using the formula,

$$n=[(Z\alpha /2+Z\beta {)}^{2}*V\_eff]/(\Delta^{2}*\rho^{2}),$$

where n is the required sample size per group; Zα/2 is the critical value of the standard normal distribution for a two-tailed test with a significance level of α; Zβ is the critical value of the standard normal distribution for a specified power (1-β) of the test; V_eff is the effective sample size, which accounts for the correlation between the repeated measures within individuals; Δ is the minimum clinically significant difference; r is the number of repeated measures; and ρ is the correlation between the repeated measures.

Assuming a conservative value of 0.5 for ρ based on previous literature [20, 21], and for an α of 5%, 1-β of 80%, r of 4, and Δ of 7 [22, 23], we can calculate the effective sample size as follows:

$$\begin{array}{l} V\_eff=n/(1+(r‐1)*\rho )\\ \;=55/(1+(4‐1)*0.5)\\ \;=22.5 \end{array}$$

Therefore, n can be calculated as follows:

$$\begin{array}{l} n=[(1.96+0.84{)}^{2}*22.5]/(7^{2}*0.5^{2})\\ \;=53.3 \end{array}$$

Thus, at least 54 participants per group must be enrolled to have 80% power to detect a minimum clinically significant difference of 7 points between the groups using GEE, with a significance level of 5%. As there are four groups in the study, a total of 216 participants (54 per group) must be enrolled. Based on our previous experience, a dropout rate of 16% was expected; to account for this, we aim to recruit a total of 256 participants, with 64 participants per group.

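### The continued-practice analysis (Table 1, third row) pairs a status that can change between visits with repeated-measures ANOVA on subgroups, and its stated conclusion about sustained practice does not follow on either reading

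*Protocol article*

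**What the plan says.** The third row of Table 1 asks whether continued practice influences the effect of the interventions. Its hypothesis names two changes from baseline, to the 40-day and to the 1-year visit: "The decrease from baselines to delayed post-intervention and long-term follow-up Kessler psychological distress scale scores will be significantly larger in all intervention groups" among those who keep practising than among those who do not. The analysis cell has two sentences. The first forms the groups: "Participants in each group will be subdivided based on whether or not they continued practice during each follow-up". The second names the test: "Repeated measures analysis of variance will be conducted on the subgroups".

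The section Outcomes and measures says when status is obtained: "At the immediate post-intervention, delayed post-intervention, and long-term follow-up measurements, apart from the K10". It also says how, namely by a question: "the participants will be asked if they have continued practicing the techniques learned during the intervention". Status is thus a self-report, taken after randomisation, at three visits and in the same session as the outcome.

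The interpretation cell commits to a reading in both directions. A positive result is to mean that keeping up the practice adds to well-being. A null result is to mean that it plays no important part. The article's statistical analysis plan sections do not return to continued practice. They plan GEE with robust standard errors for the repeated K10 data.

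**The concern.** The grouping and the test do not fit together. An ordinary repeated-measures ANOVA with a between-person factor needs one label for a person's whole K10 series. The row forms its labels at each follow-up, and a person may be a continuer at 40 days and not at 1 year. The cell does not say whether one ANOVA or several are meant, or how a person who switches is classed.

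The obvious repair, one split and one ANOVA per follow-up, leaves a second problem. Continuers select themselves, and they report practice and distress together. Someone who feels better may be more likely to keep practising, or to say so.

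Both pre-stated conclusions are exposed. Dilution makes a null result unsafe evidence that practice does not matter. Selection on current distress makes a positive result unsafe evidence that it does.

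**Working it through.** The row gives no figure of its own to reproduce beyond the common arm size: "Thus, at least 54 participants per group must be enrolled to have 80% power". The 54 is used here only as an arm size. The threshold is the plan's: "Statistical significance will be set at a two-tailed p < 0.05". The visit correlation of 0.5 and the 7-point difference come from the sample size section. Rates of practising, stopping and restarting are not in the document and are assumed.

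**1. One label carried over all visits.** Let *s* be the share of 40-day continuers who stop by 1 year and *r* the share of non-continuers who restart. If practice acts on K10 at the same visit, the 40-day label applied to the 1-year change keeps a fraction 1 − *s* − *r* of the true contrast:

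| *s* | *r* | fraction kept |
|---|---|---|
| 0 | 0 | 1.00 |
| 0.10 | 0 | 0.90 |
| 0.30 | 0 | 0.70 |
| 0.50 | 0 | 0.50 |
| 0.50 | 0.20 | 0.30 |

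For the 1-year label on the 40-day change, the fraction is P(continuer at 40 days | continuer at 1 year) − P(continuer at 40 days | non-continuer at 1 year). Take 50% continuing at 40 days, *s* = 0.40 and *r* = 0.10:

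- Continuing at 1 year: 0.5 × 0.6 + 0.5 × 0.1 = 0.35.
- Fraction: 0.30/0.35 − 0.20/0.65 = 0.857 − 0.308 = 0.55.
- A 7-point contrast becomes about 3.9 with the 1-year label on the 40-day change, and 0.5 × 7 = 3.5 with the 40-day label on the 1-year change.
- Switchers: 54 × (0.5 × 0.4 + 0.5 × 0.1) = 13.5 per arm.

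Over 30% to 70% continuing at 40 days and the switching rates tried, this second fraction runs from 1.00 down to 0.26.

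**2. Each follow-up's status paired with the change to that follow-up.** The fraction is 1.00 whatever the switching. Simulation recovered 7.00 of 7 points at both visits.

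**3. The per-visit comparison when practice has no effect.** Assume arms of 54, correlation 0.5, and log-odds of reporting practice that rise by 0.5 to 0.75 for each SD of lower current K10. Continuers and non-continuers then differ significantly in K10 change in about 12% (0.5) to 21% (0.75) of arms, against a nominal 5%. Variants of the set-up gave 10% to 22%.

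Baseline adjustment does not cure this. If current K10 differs by δ SD, baseline differs by about 0.5δ.

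- Change score: gap of 0.5δ against an SD of √(2 × 0.5) = 1, a ratio of 0.5δ.
- Baseline-adjusted: gap of about δ − 0.5 × 0.5δ = 0.75δ against an SD of √(1 − 0.25) = 0.87, a ratio of about 0.87δ.

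So the adjusted contrast can show the selection more strongly.

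**4. A lagged alternative.** Regressing 1-year K10 on 40-day practice, adjusted for baseline and 40-day K10, holds the false-positive rate near 5% in the same set-up. It answers a different question, however. With correlation 0.5, each earlier K10 has weight 0.5/1.5 = 1/3. Adjusting for a 40-day K10 that practice has already lowered therefore removes 1/3 of the effect. Suppose 50% practise at 40 days and 30% at 1 year:

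- Nested statuses: the label carries 0.3/0.5 = 0.60, leaving 0.60 − 0.33 = 0.27 of a same-visit effect (about 26% in simulation).
- Independent statuses: 0 − 0.33 = −0.33, the wrong sign.

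**The case against.** The strongest reply is that the row already means one split and one comparison per follow-up. Its hypothesis names two separate changes, and the split is made at each follow-up. Each ANOVA would then have one fixed label per person, and nothing would be misattributed. This stands. A reader might infer that the plan credits K10 change to the wrong practice status, but the text does not fix that. The loss in step 1 arises only if a label is carried across visits, and its size rests on unstated switching rates.

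A reader might also take ANOVA on the subgroups to mean separate tests of time inside continuers and inside non-continuers, so that the two are never compared. The interpretation cell speaks against this, because it describes a difference in decrease between the two kinds of participant.

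Three further points carry some weight. The question asks about practice already continued, so it looks back over a period before the session. The false-positive rates depend on an assumed link between current distress and reported practice. The row is not among the primary comparisons, and an article may leave model coding to a fuller plan.

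None of this rescues the conclusion. A retrospective answer given alongside the K10 does not establish which came first. The causal wording, for positive and null results alike, is printed in the row and not left to another document.

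**Conclusion.** The point holds in a limited form. As written, the row does not define a workable analysis for a status that changes. A single ANOVA over all visits would misclassify switchers, keeping 0.70 of the contrast at 30% stopping and 0.50 at 50% stopping with no restarting. Separate ANOVAs per follow-up have no such loss. They remain comparisons of self-selected groups, with a false-positive rate of about 12% to 21% per arm of 54 under the assumed log-odds of 0.5 to 0.75 per SD. The two figures belong to different readings and must not be added together.

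On neither reading does the result show that sustained practice contributes to well-being, or that it does not. The randomised comparisons against control are not touched by this point. It should be corrected, but it does not threaten the primary analysis.

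**What to change.** Replace the subgroup ANOVAs in this row with one GEE model in the three active arms:

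- Enter practice as a visit-specific covariate, with adjustment for arm and baseline K10, using all available visits.
- Pair each follow-up's practice status with the K10 change to that same follow-up.
- Test the difference in change between continuers and non-continuers directly, at 40 days and at 1 year.
- For this model, use an independence working correlation with the robust standard errors already planned. An exchangeable structure would mix one visit's practice with another visit's K10.

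Reword the interpretation cell so that a positive and a null result are both described as a non-randomised association. The model does not remove selection on current distress (step 3 of the working), so this wording is an essential part of the change.

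The regression of 1-year K10 on 40-day practice, adjusted for baseline and 40-day K10, may be added as a sensitivity check on reverse causation only. It should not replace the main model, because it does not recover a same-visit practice effect.

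Cost: two cells of Table 1 reworded, one model and an optional check, and no new data. The section on ethical considerations already foresees a version 2 of the protocol. The price is a weaker claim and slightly more analysis work.

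### Table 1, third row, reads a non-significant split by continued practice as showing no role for practice, and prints beside it an 80% power derived for whole arms of 54, not for parts of one arm

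*Protocol article*

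**What the plan says.** All of this is in the protocol article, mainly Table 1, third row (continued practice).

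- **Analysis cell:** "Participants in each group will be subdivided based on whether or not they continued practice during each follow-up". The test named for this split is given as: "Repeated measures analysis of variance will be conducted on the subgroups".
- **Sampling cell:** "54 participants each in the Bhagavad Gita group, Kuchipudi dance group, Both Bhagavad Gita and Kuchipudi dance group, and Control group for 80% power", with alpha at 5%. The other three rows carry the same text.
- **Interpretation cell:** the trigger is a null comparison, worded "if there are no significant differences in the decrease of the Kessler psychological distress scale scores between participants who continue and those who do not". The conclusion that the cell attaches to such a result is that "it would indicate that continued practice does not play a significant role in the effectiveness of the interventions".
- **Sample size calculation:** 54 per group is the number needed for "80% power to detect a minimum clinically significant difference of 7 points between the groups using GEE", that is, between randomised arms. The recruitment target is 64 per arm to allow for 16% dropout.
- **Data analysis:** "Statistical significance will be set at a two-tailed p < 0.05".

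The row gives no equivalence margin, no confidence-interval criterion, no expected share of continuers and no power for the split. The post-hoc power analyses in the other three rows concern subgroups by age, religion, education and employment. They are not mentioned for this question.

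**The concern.** There are two linked faults in the written text.

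First, failing to reject a null hypothesis does not show that the null is true. The row turns p > 0.05 into a substantive answer (practice plays no significant role) without asking which differences the data can exclude. That is invalid at any sample size, and it misleads most when the comparison is small.

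Second, the 80% power printed beside this question belongs to a different comparison. The 54 is a whole arm. In this row the two groups compared add up to 54. A reader who trusts the printed power would take a null result as fairly strong evidence against an association, which it may not be.

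At stake is a statement that keeping up the practice does not matter, made when the data may be compatible with a difference as large as the plan's own minimum clinically significant one.

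**Working it through.** **Inputs from the article.** 54 analysed per arm, Δ = 7 K10 points, two-sided α = 0.05, claimed power 80%, ρ = 0.5, each arm split by practice status.

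**Assumed, because the article gives neither.** The SD of the K10 change (7, 10, 14, and the value implied below) and the split (27/27 and 11/43).

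**1. The plan's own figure.** The printed formula gives (1.96 + 0.84)² × 22.5 / (7² × 0.5²) = 176.4 / 12.25 = 14.4, not the 53.3 shown; V_eff as printed is 55 / 2.5 = 22.0, not 22.5. That is a separate matter. Here I take the claim at face value: 54 per arm, 80% power, 7 points. In a standard two-means calculation, n = 2 × (2.8)² × SD² / 7². With SD 13 this is 2 × 7.84 × 169 / 49 = 54.1, so the claim corresponds to an SD of about 13.

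**2. Same difference, one arm instead of two.** The standardised signal for 80% power is 1.96 + 0.84 = 2.80, and it scales with 1/√(1/n₁ + 1/n₂).

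- 54 v 54: √(2/54) = 0.192, signal 2.80, power 80%.
- 27 v 27: √(2/27) = 0.272, signal 2.80 × 0.192/0.272 = 1.98, power Φ(1.98 − 1.96) = about 51%.
- 11 v 43: √(1/11 + 1/43) = 0.338, signal 2.80 × 0.192/0.338 = 1.59, power Φ(1.59 − 1.96) = about 36%.

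The non-central t at SD 13 agrees: a 7-point difference is missed 51% of the time at 27/27 and 65% at 11/43. This step needs no outside SD, only the plan's own power claim.

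**3. Range over assumed SDs.** Two-sample t-test on one change score, 54 analysed, no multiplicity correction. Chance of missing 7 points:

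| SD of change | 27/27 | 11/43 |
|---|---|---|
| 7 | 5% | 17% |
| 10 | 29% | 47% |
| 14 | 56% | 69% |

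**4. Detectable difference at 80% power** (non-central t): about 0.78 SD at 27/27 and about 0.96 SD at 11/43.

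**5. Allowance for the planned model.** The row plans repeated measures analysis of variance, not a single-score t-test. With ρ = 0.5 and equal variances σ², one change score has variance 2σ²(1 − 0.5) = σ². The mean of two follow-ups minus baseline has variance 0.75σ² + σ² − σ² = 0.75σ². If practice status is the same at both follow-ups, the even-split miss rate at SD 14 falls from 56% to about 45%.

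**6. Interval width.** The 95% half-width is 2.007 × SD × √(1/n₁ + 1/n₂). At SD 10 it is 5.5 points at 27/27 and 6.8 at 11/43. At SD 13 it is 7.1 and 8.8, wider than the 7-point margin itself.

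**The case against.** **The figures rest on assumptions.** This is correct. Effect size, SD and split are all the reviewer's. At SD 7 the comparison would have 95% power at an even split and 83% at 11/43. A reader might infer that non-significance is the most likely outcome here, or that the split will usually miss a moderate difference. The documents do not support that: at SD 7 or 10 every miss rate in the table above is below one half. Figures such as 56% to 82% for a 0.5-SD difference reproduce arithmetically, but they use an effect that is not the plan's (0.5 SD equals 7 points only at SD 14), and the top end needs a 5/49 split that nothing in the article suggests.

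**The t-test is not the planned model.** This also stands, and pooling follow-ups lowers the miss rates somewhat. It does not remove the loss from splitting one arm, and the scaling in step 2 starts from the plan's claimed power.

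**The arms might be pooled.** Pooling the three active arms (162 people) would cut the miss rate for 0.5 SD to 12% at 81/81. But the row subdivides participants within each group and says nothing of pooling.

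**The wording is hedged.** A *significant role* could mean statistical significance only. But the sentence is offered as the answer to whether practice influences the effect, and is set against the reading that sustained practice contributes to well-being. It works as a negative conclusion.

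**It is a minor question.** It is one of four, and the Primary analysis and Subgroup analyses sections do not list it. The dissemination plan is general and does not mention this result. That limits the consequence, but does not make the rule valid.

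**Conclusion.** The point holds in this form. The third row of Table 1 treats non-significance as evidence of no role, and states a power that does not belong to its comparison. Both are in the text as written, and no other section repairs them.

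On the plan's own claim of 80% for 54 against 54, a 7-point difference within one arm has about 50% power at best and about 35% at 11/43. Beyond that the size is conditional: miss rates run from 5% to 69% over assumed SDs of 7 to 14 and the two splits shown, and are somewhat lower if follow-ups are pooled. Confidence is high that the inference rule and the printed power are wrong. It is not high for any one miss rate. This should be corrected, but it does not affect the primary between-arm analysis.

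**What to change.** Reword two cells in the third row of Table 1.

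1. **Sampling cell.** Delete the 80% power claim, or replace it with the difference detectable at stated, assumed splits: about 0.8 SD at 27/27 and about 1.0 SD at 11/43.
2. **Interpretation cell.** Commit to reporting the continuer minus non-continuer difference in K10 decrease with its 95% confidence interval, and state that a non-significant result is inconclusive.
3. **Optional.** If a negative statement is wanted, reserve *no relevant association* for an interval lying wholly inside a pre-stated margin, such as the plan's 7 points.

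**Cost.** No new data or analysis. The stated power becomes less favourable, and the row will probably end as inconclusive unless the SD is small. The optional rule is demanding: in simulation with a true difference of zero and 54 analysed, it is met about 43% of the time at SD 10 with 27/27, about 10% at SD 10 with 11/43, and about 6% or less at SD 13. If that is too rarely useful, items 1 and 2 alone correct the fault.

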## Introduction

The COVID-19 pandemic has had a profound impact on the mental health of people experiencing homelessness (PEH) [1, 2] PEH have reported increased rates of anxiety, depression, and post-traumatic stress disorder [1, 2], with a significant proportion suffering from severe mental illness and chronic substance use [2]. Moreover, social isolation during the pandemic has been associated with heightened anxiety and depression symptoms among PEH [2]. Substance use, which is prevalent in this population, can further worsen mental health outcomes [2, 3].

The World Health Organization (WHO) defines mental health as a state of well-being, encompassing an individual’s ability to realize their potential, cope with life’s challenges, work productively, and contribute to their community [4]. Recognizing the importance of mental health, the WHO has advocated for integrating mental health support into the global response to the COVID-19 pandemic [5]. General guidance from the WHO on integrating mental health support into the pandemic response which can be applied to PEH includes providing social support, accurate information, and addressing stigma and discrimination.

Samanjasa Foundation has been actively engaged in providing services to PEH in Chennai, Dhanbad, Bhubaneshwar, and Hyderabad, India, for the past decade. These services include offering meals, upskilling opportunities, recreational activities, and linkages to government schemes and employment prospects. During the COVID-19 lockdown in India, we continued to support PEH by providing online recreational and upskilling activities. However, due to logistical challenges, we were unable to resume face-to-face sessions after the lockdown was lifted. Throughout our interactions with PEH, we observed an increase in psychological distress during and after the pandemic. To address this issue, we decided to augment our usual recreational activities, such as Kuchipudi dance classes [6], with an emic intervention involving imparting the teachings of the Bhagavad Gita through online platforms [7].

Engaging in hobbies has been shown to effectively reduce stress, foster social connections, and restore a sense of self among PEH [8, 9]. However, many of our clients have been unable to participate in recreational activities due to their daily struggles to earn a living, despite expressing a desire to engage in hobbies. Therefore, we sought a brief intervention that could enhance the coping abilities of PEH.

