Does learning the Bhagavad Gita provide any added benefit to people experiencing homelessness who are engaging in a recreational activity in terms of reducing their psychological distress	The decrease from baselines to immediately post-intervention, delayed post-intervention, and long-term follow-up Kessler psychological distress scale scores will be significantly larger in the Both group than the Bhagavad Gita and Kuchipudi dance groups	54 participants each in the Bhagavad Gita group, Kuchipudi dance group, Both Bhagavad Gita and Kuchipudi dance group, and Control group for 80% power and 5% alpha	Intergroup differences will be analysed by the generalised estimating equation and analysis of covariance with continued practice and religion as covariates. Subgroup analyses will be conducted by stratifying the participants in each group by age, religion (Hindu, Non-Hindu), educational attainment, and employment. Post-hoc power analyses will be conducted to verify the robustness and reliability of the subgroup analyses	If the reduction in the Kessler psychological distress scale scores is highest in the Both group, it would suggest that learning the Bhagavad Gita combined with engaging in a recreational activity may offer additional benefits in reducing psychological distress among homeless persons compared to learning the Bhagavad Gita group or engaging in a recreational activity alone. This finding would indicate that the combination of the intervention has a more substantial effect on decreasing distress levels

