### Interventions

The participants in the Gita group will be imparted the teachings of the second chapter of the Bhagavad Gita (all verses) for 1 week, for 60 minutes per day. The teachings of the Bhagavad Gita will be imparted by a trained teacher and the second chapter has been chosen as it is said to contain the essence of the entire Bhagavad Gita [16]. The participants in the Kuchipudi group will be taught the Kuchipudi dance choreography to a popular devotional song (“Sivashtakam”, choreographed by Padma Bhushan [name] [name], song duration is approximately 10 min) for 60 minutes per day by a trained teacher for 1 week. Every day for 1 week, the participants in the Both group will be taught the Kuchipudi dance choreography to a popular devotional song (“Vandanamu Raghunandana”, choreographed by Kala Tilakam [name], song duration is approximately 5 min), which is shorter in duration than the song used in the Kuchipudi group, for 30 minutes by a trained teacher, followed by imparting the teachings from selected verses of the second chapter of the Bhagavad Gita (Verse 40–72) for 30 minutes by a trained teacher. The participants in the control group will receive no intervention. The participants will be instructed to join their assigned groups at the scheduled meeting times using the meeting link in their sealed envelopes. Apart from the teaching sessions, meetings will also be scheduled one day before the start of the teaching sessions, one day after the end of the teaching sessions, 40 days after the end of the teaching sessions, and 1 year after the end of the teaching sessions for the purpose of recording the baseline, immediate post-intervention, delayed post-intervention, and long-term follow-up measurements, respectively. For participants in the control group, the meeting schedule will consist of only the four measurement sessions.

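### Table 1's fourth question asks what the Gita adds to recreation, but the Both arm swaps half the dance for a shortened Gita course, and the row's hypothesis and interpretation do not fit the question

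*Protocol article*

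**What the plan says.** Table 1 in the Introduction sets out four questions, each with a hypothesis, a sampling plan, an analysis and an interpretation. The fourth asks: "Does learning the Bhagavad Gita provide any added benefit to people experiencing homelessness who are engaging in a recreational activity". Its hypothesis is that the fall in K10 will be "significantly larger in the Both group than the Bhagavad Gita and Kuchipudi dance groups". Its interpretation cell begins "If the reduction in the Kessler psychological distress scale scores is highest in the Both group", and in that case suggests a possible extra benefit of the combination over either component alone. It does not say what follows if that condition is not met.

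The Interventions section fixes the arms. Kuchipudi participants are taught one choreography "for 60 minutes per day by a trained teacher for 1 week", to a song of about 10 minutes. Gita participants study every verse of the second chapter, also for 60 minutes a day over a week. Both participants learn a different song of about 5 minutes, "which is shorter in duration than the song used in the Kuchipudi group". They are taught it "for 30 minutes by a trained teacher, followed by imparting the teachings from selected verses of the second chapter of the Bhagavad Gita", limited to verses 40–72, which also takes 30 minutes.

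As background, the Introduction reports a service decision in add-on terms: "we decided to augment our usual recreational activities, such as Kuchipudi dance classes [6], with an emic intervention".

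**The concern.** The question is about adding: given that someone already dances, does the Gita help further? An arm that answers it directly would keep the dance programme whole and put the Gita on top. The Both arm halves the dance, changes the song and gives part of the Gita course. Its difference from Kuchipudi mixes a gain from the Gita with a loss from reduced dance.

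The other two cells of the row do not fit the question either. The hypothesis needs Both to beat Gita as well as Kuchipudi, and beating Gita is about what dance contributes. The interpretation needs only that Both has the largest reduction, a looser condition than the significant superiority in the hypothesis.

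At stake is the answer to one yes/no question. Table 1 exists to fix readings before the data are seen, so its wording governs what may later be concluded about added benefit.

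**Working it through.** **1. The arms side by side** (Interventions; seven daily sessions assumed for one week)

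| Arm | Dance per day | Gita per day | Content | Week total |
|---|---|---|---|---|
| Kuchipudi | 60 min | 0 | song of about 10 min | 7 × 60 = 420 min dance |
| Gita | 0 | 60 min | all verses of chapter 2 | 7 × 60 = 420 min Gita |
| Both | 30 min | 30 min | different song of about 5 min; verses 40–72 | 7 × 30 = 210 min of each |

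Verses 40–72 are 72 − 40 + 1 = 33 verses, so at least the 39 before them are left out. Moving from Kuchipudi to Both removes 210 minutes of dance, changes the song and adds 210 minutes of a partial Gita course. No arm is full dance plus Gita.

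**2. What each contrast estimates**

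Assumptions, none of them in the protocol: D and G (both ≥ 0) are the K10 reductions against control from the full dance and full Gita programmes; a halved component keeps a share f ≤ 1 of its effect; f is the same for both components; the components do not interact. Then:

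- Both = f(D + G)
- Both − Kuchipudi = f(D + G) − D = G − (1 − f)(D + G)
- Both − Gita = f(D + G) − G = fD − (1 − f)G

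The add-on effect the question asks about is G. In this model Both − Kuchipudi falls short of it by (1 − f)(D + G), and is positive only if f > D/(D + G).

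**3. Illustration with G = 7** (the difference named in the sample size calculation)

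| D | f | Both − Kuchipudi | Both − Gita |
|---|---|---|---|
| 7 | 0.5 / 0.75 / 1 | 0 / 3.5 / 7 | 0 / 3.5 / 7 |
| 3.5 | 0.5 / 0.75 / 1 | 1.75 / 4.375 / 7 | −1.75 / 0.875 / 3.5 |
| 0 | 0.5 / 0.75 / 1 | 3.5 / 5.25 / 7 | −3.5 / −1.75 / 0 |

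In every row Gita truly adds 7 points to dance. At f = 1 the Kuchipudi contrast shows no shortfall. At D = 0, Both does not beat Gita at any f, so the row's hypothesis is untrue although the answer to the question is yes. That holds at f = 1 too, so it does not depend on loss of dose.

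**4. Chance of a significant win for Both over Kuchipudi**

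The protocol claims 80% power at 7 points with 54 per group. Its printed formula does not reproduce that sample size: (1.96 + 0.84)² × 22.5 / (7² × 0.5²) = 176.4 / 12.25 = 14.4, against the stated 53.3. No SD is given. The 80% is therefore only taken at face value and scaled. It implies a noncentrality of 1.960 + 0.842 = 2.802 at 7 points, so at d points the chance is Φ(2.802 × d/7 − 1.960):

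- d = 0: 2.5%
- d = 1.75: 10%
- d = 3.5: 29%
- d = 4.375: 42%
- d = 5.25: 56%
- d = 7: 80%

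The planned Bonferroni correction would lower all of these.

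**5. Hypothesis against interpretation**

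The hypothesis asks for "significantly larger in the Both group than the Bhagavad Gita and Kuchipudi dance groups"; the interpretation starts from "If the reduction in the Kessler psychological distress scale scores is highest in the Both group". The second can be met by a numerical ranking with neither pairwise difference significant.

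**The case against.** Equal contact time is a sound choice. With 60 minutes a day in all three active arms, a win for Both cannot be put down to extra teaching, whereas a 60 + 30 arm would confound the Gita with contact. The Patient and public involvement statement says participants were consulted on burden. The interpretation cell is hedged and already speaks of the combination against either component alone, which is close to what the arms deliver. All of this stands, and it is why the arms should stay. If both components help or are neutral and do not interact, a significant win over Kuchipudi still supports added benefit in direction, subject to the changed song and verses.

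A reader might infer that the plan will report a null here as no added benefit. The text does not say so. Row 4 gives no reading of a null, and row 2 gives none either. Row 3 does, saying of non-significance that "it would indicate that continued practice does not play a significant role in the effectiveness of the interventions", but that is about continued practice and cannot be carried over. Nor does the Introduction's remark about augmenting usual activities define this comparison; it describes what the organisation decided to offer.

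The figures are also open to challenge. The 0-point and 2.5% results need D = G = 7, f = 0.5 and no interaction. The shorter song and fewer verses suggest content was scaled to the time, and nothing in the protocol shows whether f is nearer 0.5 or 1. Synergy is assumed away. The power base does not reproduce. The numbers show what is possible and do not predict the result.

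**Conclusion.** The concern holds as a mismatch within stated text. The fourth question asks for an add-on effect; the arms give a time-matched substitution contrast. The hypothesis includes a comparison that concerns dance and can fail while the Gita does add to dance. The interpretation is tied to rank, where the hypothesis is tied to significance. The first and third of these follow from the wording alone; the second needs only one plausible case, such as dance having no effect.

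The size of any understatement is unknown. In the illustration it runs from none (f = 1) to the whole 7 points (D = G = 7, f = 0.5), resting on an assumed dose-response and no interaction. The reach is modest: one secondary question. Each arm against control, and Gita against Kuchipudi, are unaffected.

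**What to change.** Keep the arms and the analysis, and reword row 4 of Table 1:

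- **Question:** whether a combined programme of 30 minutes of dance and 30 minutes of Gita a day lowers K10 more than 60 minutes a day of dance alone or of Gita alone.
- **Interpretation:** read Both minus Kuchipudi and Both minus Gita separately, each on its multiplicity-adjusted test, in place of the ranking. Note that only the first bears on what the Gita contributes, and that song and verses also differ between arms.
- **Null:** state in advance that a non-significant Both-minus-Kuchipudi result does not exclude an add-on benefit of the Gita.

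The cost is a narrower claim on one secondary question. No arm, test or sample size changes, and the wording can be settled before results are seen.
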